## Abstract

**Background:**

Psilocybin may help treat obsessive–compulsive disorder (OCD). To date, only one open-label study of psilocybin for OCD exists, necessitating further investigation with a randomized controlled design. The neural correlates of psilocybin’s effects on OCD have also not been studied.

**Objectives:**

This first-of-its-kind trial aims to evaluate the feasibility, safety, and tolerability of psilocybin in the treatment of OCD, provide preliminary evidence on the effects of psilocybin on OCD symptoms, and elucidate neural mechanisms that may mediate psilocybin’s effects on OCD.

**Design:**

We use a randomized (1:1), double-blind, placebo-controlled, non-crossover design to examine the clinical and neural effects of either a single dose of oral psilocybin (0.25 mg/kg) or active placebo-control agent (250 mg of niacin) on OCD symptoms.

**Methods and analysis:**

We are enrolling 30 adult participants at a single site in Connecticut, USA who have failed at least one trial of standard care treatment (medication/psychotherapy) for OCD. All participants will also receive unstructured, non-directive psychological support during visits. Aside from safety, primary outcomes include OCD symptoms over the past 24 h, assessed by the Acute Yale-Brown Obsessive–Compulsive Scale and Visual Analog Scale ratings. These are collected by blinded, independent raters at baseline and the primary endpoint of 48 h post-dosing. Total follow-up is 12 weeks post-dosing. Resting state neuroimaging data will be collected at baseline and primary endpoint. Participants randomized to placebo will be offered the chance to return for an open-label dose of 0.25 mg/kg.

**Ethics statement:**

All participants will be required to provide written informed consent. The trial (protocol v. 5.2) was approved by the institutional review board (HIC #2000020355) and registered with ClinicalTrials.gov (NCT03356483).

**Discussion:**

This study may represent an advance in our ability to treat refractory OCD, and pave the way for future studies of neurobiological mechanisms of OCD that may respond to psilocybin.

## Introduction

1.

### Background and rationale

1.1.

Obsessive–compulsive disorder (OCD) has a lifetime (to date) prevalence and morbid risk of 2.3 and 2.7%, respectively (1). OCD is characterized by obsessions (recurrent, intrusive thoughts, images, or impulses that induce significant anxiety or distress) and compulsions (repetitive and/or ritualized physical or mental actions undertaken in an attempt to reduce that anxiety or distress). As OCD progresses, it is often disabling and chronic (2–4), partly due to long latencies to treatment (5).

If treated, selective serotonin reuptake inhibitors (SSRIs) are the first-line pharmacological option. Although SSRIs have been shown to be efficacious across randomized placebo-controlled trials (6), most patients do not show significant response until at least 2 weeks of continuous treatment (7), and up to 60% of patients do not respond (8–10). Cognitive-behavior therapy (CBT) with exposure and response prevention (ERP) is the first-line psychological treatment (11–14). However, access to appropriately trained therapists remains limited (15–19). Further, many OCD patients classified as responders in SSRI and CBT/ERP trials remain symptomatic and lead restricted lives (20). Relapse after SSRI discontinuation or completion of CBT is also common (21, 22). While neurosurgery is an option for severe, treatment-refractory OCD (23), fundamentally novel, faster-acting, and less invasive alternatives are urgently needed.

Psilocybin is a tryptamine alkaloid prodrug found naturally in mushrooms of the genus *Psilocybe*. When ingested, psilocybin is metabolized into psilocin, which is an agonist or partial agonist at several serotonin receptors, with complex downstream effects (24, 25). Acute psychological effects of psilocin action include altered visuospatial, motion, and time perception, changes in information processing and thought content, depersonalization and derealization, dizziness, impaired concentration, profound positive and negative emotions and mood lability, and paresthesia (26). Common acute physiological effects are related to sympathetic nervous system activation (e.g., changes in body temperature, increases in blood pressure or heart rate) (27, 28). These effects, both psychological and physiological, are transient, typically lasting no longer than 6 h after psilocybin administration (26, 28). The majority of individuals receiving psilocybin in controlled settings maintain insight into the nature and source of their experiences. No convincing evidence exists for symptoms of hallucinogen persisting perception disorder (HPPD) when psilocybin is administered in controlled research settings. Additionally, instances of serious adverse events (SAEs) have generally been low in these settings (29, 30).

Psilocybin dosing, paired with unstructured psychological support, has been examined in clinical trials for treatment-resistant depression, cancer-related anxiety and depression, alcohol dependence, and tobacco addiction (31). Early trials (*n* = 4) used an open-label design, while more recent trials have used a randomized controlled design (*n* = 7) (31). To date, aside from a few case reports (32–34), there has only been one small study of psilocybin in OCD (35). In that study, nine participants were each assigned to receive a dose of oral psilocybin paired with unstructured psychological support per week for 4 weeks: low (100 μg/kg), medium (200 μg/kg), then high (300 μg/kg) dose in that order, with a very low dose (25 μg/kg) randomly inserted, in a double-blind fashion, at some point after the first dose. That study was designed primarily to assess safety and tolerability, but clinical data were also collected. There was a significant main effect of time on OCD symptoms, with 23 to 100% reduction in Yale-Brown Obsessive Compulsive Scale (Y-BOCS) (36, 37) scores 24 h after dosing, well beyond both the expected pharmacological life of psilocybin. Other than transient hypertension in one participant, no SAEs were observed. One participant maintained full symptom remission at 6-month follow-up. The authors speculated on the mechanisms underlying the effects of psilocybin on acute and longer-term OCD symptom improvement, including transcendental experiences that catalyze significant acute feelings of wellness, rapid 5-HT receptor down-regulation, and sustained, adaptive changes in metacognitive processes (e.g., attention, working memory). These preliminary findings justify investigating the feasibility, tolerability, safety, and potential therapeutic effects of psilocybin on OCD more rigorously with a randomized, double-blind, placebo-controlled design. We present such a trial here.

An additional aim of the present study is to examine neural correlates of psilocybin effects in OCD. Neuroimaging studies of psilocybin in healthy participants have highlighted acute neural effects on areas implicated in OCD pathophysiology. A functional magnetic resonance imaging (fMRI) study of psilocybin administration in healthy controls showed acute decreases in blood oxygen level-dependent (BOLD) signal and cerebral blood flow (CBF) in fronto-temporo-parietal regions and the connectivity hubs of thalamus, putamen (striatum) and midline cortex (anterior and posterior cingulum) (38), areas which are hyperactive in OCD. Acute decreased activity in the anterior cingulate cortex (ACC) and medial prefrontal cortex (mPFC) predicted the intensity of acute subjective effects of psilocybin, and subsequent mPFC seed connectivity analysis showed that psilocybin infusion was related to acute reduced connectivity between the posterior cingulate cortex (PCC) and mPFC (39). Additionally, a preclinical study showed that psilocybin facilitates acute extinction of classically conditioned fear responses and increases hippocampal neurogenesis (40). These results may have clinical implications for psilocybin-facilitated extinction learning in OCD, given that extinction recall and associated neural activation in the vmPFC are blunted in patients with OCD (41). In summary, psilocybin appears to acutely modulate brain activity in OCD-relevant regions in healthy controls (42). In light of these findings, the present study aims to explore the neuronal correlates of potential therapeutic effects of psilocybin on OCD symptomatology, albeit in the post-dosing period. Functional imaging studies of SSRI treatment offer a precedent for treatment-induced connectivity changes linked with symptom improvement. For example, SSRI pharmacotherapy in depression (43) and OCD (44) have been shown to “normalize” aberrant connectivity in key brain regions (particularly the default mode network). Given that the medial prefrontal cortex and the striatum are centrally implicated in OCD and appear directly modulated by psilocybin, we considered frontostriatal connectivity a promising target for psilocybin’s potential theraputic effects.

### Objectives and hypotheses

1.2.

This trial aims to evaluate the feasibility of a placebo-controlled study of single-dose psilocybin in the treatment of OCD, to evaluate safety and tolerability, to provide initial evidence as to the effects of oral psilocybin on OCD symptomatology, as well as provide initial data on the neural mechanisms that may mediate psilocybin’s purported therapeutic effects on OCD.

To do so, we will use a randomized, double-blind, niacin placebo-controlled, non-crossover study design, coupled with pre-post-dosing fMRI. The choice of a single dose – as opposed to multiple administrations, as in Moreno et al. (35) – was balanced with considerations of the addition of a neuroimaging component with repeat scanning, an increase in target sample size, the use of a randomized controlled design, available budget, and the need to focus our research questions.

To investigate the effects of oral psilocybin compared to placebo on OCD symptom severity, we set the primary endpoint as 48 h post-dosing. This endpoint was selected to mitigate the possibility of sleep difficulties the night of dosing interfering with ratings and scans the next day. We hypothesize that psilocybin will lead to greater OCD symptom improvement than placebo at 48 h post-dosing. We will also track safety, tolerability, and feasibility metrics throughout the study. Additionally, we will explore the interrelationships among psilocybin-induced changes in resting-state brain connectivity and OCD symptoms. Several studies indicate that abnormal frontostriatal connectivity is central to the pathophysiology of OCD, and these regions are also affected by psilocybin. We hypothesize that at 48 h post-dosing, compared to placebo: (a) psilocybin will normalize abnormal frontostriatal functional connectivity in patients with OCD; and (b) normalization of frontostriatal functional connectivity will correlate with improvement in OCD symptomatology after psilocybin dosing. Lastly, to explore effects on constructs beyond OCD, we will examine differences between psilocybin and placebo in changes on various secondary symptom and personality measures from baseline to 48 h post-dosing.

## Method

2.

### Trial design and setting

2.1.

This study (NCT03356483) will utilize a single-site, randomized (1:1), double-blind, active placebo-controlled, non-crossover design to examine the clinical and neural effects of either a single dose of oral psilocybin (0.25 mg/kg) or active placebo-control agent (250 mg of niacin) on OCD symptoms. Consistent with prior research (35, 45), unstructured, non-directive psychological support will be provided during the dosing session, as well as during two pre-dosing preparatory visits over the two consecutive days immediately before blinded dosing, and during four integration/follow-up visits (i.e., at 48 h, 1, 2, and 12 weeks post-dosing). The choice of unstructured, non-directive psychological support (as opposed to a more structured or manualized approach) is consistent with prior psilocybin clinical research. All preparatory and integration visits last for up to 2 h each.

This study will take place from November 2018 to June 2024 at the Yale OCD Research Clinic, housed within the Clinical Neuroscience Research Unit (CNRU) of the Connecticut Mental Health Center (CMHC) in New Haven, CT. The randomized phase of the study will be conducted as a 5-day inpatient stay on this locked, research-dedicated inpatient unit. The inpatient setting is logistically viable given the number of different study procedures to be completed per study day, as well as the medical and safety oversight afforded by an inpatient setting given the novel nature of the study. The choice of an inpatient setting was also strongly suggested by the Institutional Review Board (IRB) at the time of study development for ease of safety monitoring. While the study will be conducted on an inpatient unit, we do not require study participants to present with high acute risk; in fact, such participants are excluded from participation (see Section 2.3.2). Neuroimaging will be performed at the Yale Magnetic Resonance Research Center (MRRC), located in the Anlyan Center in New Haven, CT.

This study has undergone Yale Human Research Protection Program (HRPP) review and received IRB approval. This study has received Investigational New Drug (IND) approval (IND 134406) from the U.S. Food and Drug Administration (FDA) and is conducted under Drug Enforcement Administration (DEA) Schedule 1 research regulations.

### Population of interest and sample size

2.2.

We will recruit adult participants aged 21 to 65 years old with a primary diagnosis of OCD and a Y-BOCS score of at least 19. A Y-BOCS score of 19 indicates moderate OCD symptom severity; with the criteria for a persisting diagnosis of OCD and the failure of at least one trial of standard care treatment (see Section 2.3.2), this cutoff score allows us to characterize our intended sample as treatment-refractory. Participants will be recruited irrespective of gender, sexual orientation, and ethnoracial identity. We used Optimal Design (46) to calculate sample size for a linear mixed-effects model with α = 0.05 (two-tailed), power = 0.80, and *d* = 1.5, which indicated that a total of 30 participants would be needed to detect a significant group effect at the primary endpoint per our first aim. The projected effect size of 1.5 appears reasonable given previously observed effect sizes for controlled trials of psilocybin in the treatment of major depressive disorder (45). Since this is the first study examining pre-post psilocybin resting functional connectivity changes in OCD with a placebo-controlled design, the functional connectivity analyses are largely exploratory in nature. A placebo-controlled study of psilocybin-induced connectivity changes at rest in predefined regions among 38 healthy controls detected several significant psilocybin-linked changes in mPFC connectivity (47), with Cohen’s *d*s ranging from 0.2 to 0.3. We speculate that psilocybin-linked connectivity changes may be even more dramatic in a clinical population. Assuming an attrition rate of 20%, we plan to enroll 36 participants to ensure 30 completers. Data collection is planned from November 2018 to October 2023.

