##### Primary outcomes

2.4.1.1.

The primary outcome measures are the acute version of the clinician-administered Y-BOCS (AY-BOCS) (52) and the self-report Visual Analog Scale (VAS) for OCD symptoms (53), both of which assess OCD symptom severity over the past 24 h. These will be administered by independent raters at baseline and 24 and 48 h post-dosing. The Y-BOCS will also be administered by the same raters at baseline and 1, 2, 4, 8, and 12 weeks post-dosing.

Safety outcomes are included as primary outcomes as well. Safety measures assessed only during dosing include vitals and SUDs, and those assessed throughout the study duration include the Since Last Visit version of the C-SSRS (54), AEs, and any required changes to psychiatric or non-psychiatric medication regimens. The Since Last Visit version of the C-SSRS (54) assesses suicidal ideation severity, ideation intensity, and suicidal behavior severity (including non-suicidal, self-injurious behaviors) since the last assessment interval (i.e., the last study visit). AEs are defined as any untoward physical, social, economic, or psychological occurrence affecting participants, including any abnormal laboratory finding, symptom, reaction, or disease. An AE does not necessarily have a causal relationship with study procedures, and are graded as mild, moderate, or severe in this study. Severity of an AE is considered distinct from its “seriousness.” An AE is considered serious (i.e., SAE) if it: (1) is life-threatening; (2) results in hospitalization, disability/incapacity, a congenital anomaly or birth defect, or death; (3) requires medical or surgical intervention to prevent aforementioned outcomes; or (4) adversely affects the risk/benefit ratio of the study. Therefore, a severe AE is not necessarily an SAE.

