### Statistical analysis

2.9.

We will conduct linear mixed modeling (LMM) with restricted maximum likelihood estimation (to handle missing data) with appropriate alpha correction in SPSS to test our first hypothesis that psilocybin, compared to placebo, will improve OCD symptoms at the primary endpoint of 48 h post-dosing on the VAS for OCD symptoms and AY-BOCS. Treatment, time, and all interactions will be modeled as fixed effects. Participants will be modeled as a random effect. The time factor will be specified as baseline to 48 h post-dosing. Alpha-corrected *t*-tests will be used to probe interaction effects.

MRI preprocessing and group difference statistics will be evaluated using standard regression and general linear modeling approaches in a general-purpose MRI analysis package (QuNex), a processing platform that incorporates several state-of-the art neuroimaging tools (FSL, FreeSurfer, AFNI, SPM, PALM, and HCP-MPP) and thus offers comprehensive multimodal MRI analytic capabilities (92). To test the secondary hypothesis that at 48 h post-dosing, psilocybin, compared to placebo, will normalize frontostriatal connectivity at rest, we will conduct similar LMMs to examine the effect of psilocybin on activation of the corresponding regions. To test the secondary hypothesis that normalization of activity in these regions at 48 h post-dosing will correlate with clinical improvement in OCD symptoms (i.e., on the VAS for OCD symptoms, AY-BOCS, and Y-BOCS), we will conduct a correlational analysis with these variables.

Exploratory analyses of change in other secondary outcomes from baseline to 48 h post-dosing will be conducted using similar LMMs. Safety data will be presented as descriptive statistics. Data from the one-month post-dosing interviews will be qualitatively analyzed *via* interpretative phenomenological analysis (IPA) (93).

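### The power statement in section 2.2 (d = 1.5, alpha 0.05, 80%, N = 30) does not describe the planned primary test: 30 needs an unreported assumption, and the test uses a corrected alpha

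*Protocol article*

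**What the plan says.** Section 2.2 (Population of interest and sample size) reports the outcome of its calculation as a total, "which indicated that a total of 30 participants would be needed to detect a significant group effect at the primary endpoint". The error rates behind that total are printed as "α = 0.05 (two-tailed), power = 0.80", and the standardised effect is 1.5. The Optimal Design program was used for this, and the stated purpose was "to calculate sample size for a linear mixed-effects model". The section supports the effect by reference to controlled trials in depression: "The projected effect size of 1.5 appears reasonable". It does not say which SD standardises d, and it gives no variance components or baseline-to-48 h correlation. Section 2.1 makes allocation 1:1, so 30 means 15 per arm. Section 2.2 treats the 30 as completers: "Assuming an attrition rate of 20%, we plan to enroll 36 participants to ensure 30 completers".

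Section 2.4.1.1 names two primary symptom measures. "The primary outcome measures are the acute version of the clinician-administered Y-BOCS (AY-BOCS"), and the other is the self-report VAS for OCD symptoms. Section 2.9 analyses both by a linear mixed model "with appropriate alpha correction in SPSS to test our first hypothesis". The model has fixed terms for treatment, time and their interaction, a random participant term, and time running from baseline to 48 h. The correction is attached to this primary model. A separate sentence deals with corrected follow-up t-tests.

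**The concern.** Two things do not fit together.

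- **The inputs and the result.** A standardised difference of 1.5 is very large, and a group comparison at one time point detects it with far fewer than 30 people. Either the 80% is far too low for 30 completers, or the calculation contains an assumption that shrinks the effect and is not shown.
- **The alpha.** The sizing uses 0.05. The test that will be run uses something smaller for at least one of the two outcomes under any ordinary correction.

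What is at stake is how the result is read. Depending on what was assumed, 30 completers have nearly certain power for the planning effect, or 80% falling to about 70% once alpha is corrected. A null result means something different in each case, and section 2.2 does not let a reader tell which applies.

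**Working it through.** **Inputs.** d = 1.5, two-sided alpha 0.05, power 0.80 and N = 30 (section 2.2); 1:1 allocation (2.1); two primary symptom outcomes with a corrected alpha (2.4.1.1 and 2.9). Alpha 0.025 per outcome is my assumption (Bonferroni for two). I treat the model as having two time points, baseline and 48 h.

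**Step 1. Plain comparison at 48 h.**

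Normal approximation: n per arm = 2(1.960 + 0.842)² / 1.5² = 6.98, so 7 per arm and 14 in total.

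Exact calculation: noncentral t with 2n − 2 degrees of freedom and noncentrality d√(n/2).

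| n per arm | Noncentrality | Alpha | Power |
|---|---|---|---|
| 8 | 3.00 | 0.05 | 79.7% |
| 9 | 3.18 | 0.05 | 84.8% |
| 15 | 4.11 | 0.05 | 97.7% |
| 15 | 4.11 | 0.025 | 95.3% |

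The listed inputs therefore need 9 per arm, 18 in total. At alpha 0.025 they need 10 per arm, 20 in total. The stated 30 is not reproduced.

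**Step 2. Other standard variants at d = 1.5.**

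- One-sided 0.05: 14 in total.
- Baseline-adjusted comparison, SD multiplied by √(1 − ρ²), ρ from 0 to 0.8: 18 falling to 8.
- Power raised to 0.975: 30, but section 2.2 states 0.80.

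**Step 3. Treatment-by-time contrast.** If d is in units of the SD at one time point, the change score has SD √(2(1 − ρ)) in those units, and the effective effect is 1.5 / √(2(1 − ρ)).

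| ρ | Effective d | Total N at alpha 0.05 | Power of 30 at 0.05 | Total N at alpha 0.025 | Power of 30 at 0.025 |
|---|---|---|---|---|---|
| 0 | 1.06 | 30 | 80.1% | 38 | 70.3% |
| 0.2 | 1.19 | 26 | 88.0% | 30 | 80.5% |
| 0.3 | 1.27 | 22 | 91.8% | 28 | 85.8% |
| 0.5 | 1.50 | 18 | 97.7% | 20 | 95.3% |
| 0.7 | 1.94 | 12 | 99.9% | 14 | 99.8% |

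Zero correlation returns exactly 30, with 1.5/√2 = 1.06. Shrinking d by a reliability of 0.5 is the same arithmetic (1.5 × √0.5 = 1.06). Nothing else tried at alpha 0.05 and power 0.80 gives 30. At alpha 0.025, ρ = 0.2 also gives 30, but 0.025 is not the alpha that section 2.2 states.

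**Step 4. Effect of the corrected alpha on 30 completers, d = 1.5.** Plain comparison: 97.7% becomes 95.3%. Zero-correlation contrast: 80.1% becomes 70.3%, and 38 completers would be needed to restore 80%.

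**The case against.** The strongest reply is that the wrong test is being checked. Section 2.2 says the calculation was for a mixed model, and section 2.9 plans a treatment-by-time term. A sample size for that term needs a correlation or variance components, so the three listed inputs were never the full set. One conservative choice gives exactly 30. This stands. A reader might infer that the plan contains an arithmetic error and should say 18; the documents do not support that.

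Second, a journal article condenses a longer protocol that is not shown, and leaving variance components to that document is normal. This also stands: their absence alone is not the point. The point is that the figures section 2.2 does print are offered as the power of a test that section 2.9 runs at a different alpha.

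Third, the two halves do not both do full damage. If the plain comparison was meant, the corrected alpha leaves power near 95%, well above 80%. If the zero-correlation contrast was meant, 30 is right at 0.05 and only the alpha is at fault. This is correct and limits the severity.

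Fourth, 0.025 is not in the documents. The correction is unspecified, may be set in an analysis plan not shown, and under a stepwise method would not put every test at 0.025. So the 70% is conditional. That sizing and analysis use different alphas does not depend on it.

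**Conclusion.** The pairing of 80% power with alpha 0.05 does not describe the planned primary test on either main reading. For d = 1.5, 30 completers have about 98% power in a plain 48 h comparison (95% at an assumed alpha of 0.025). In the zero-correlation treatment-by-time contrast they have 80% at 0.05 and about 70% at 0.025. Intermediate correlations fall between these.

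Two stronger conclusions are tempting and not supported. One is that the trial is underpowered at 70%; that needs both zero correlation and a Bonferroni split, and neither is stated. The other is that 30 completers really give 80% power for d = 1.06 and 98% for d = 1.5. That is true only for the plain comparison. In the variant that reproduces 30, d = 1.5 in single-time-point units has 80% power, and 1.06 is the same effect expressed in change-score SDs.

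The results assume 15 completers per arm and, for the contrast, two time points. This is a minor to moderate reporting error. It does not invalidate the sample size.

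**What to change.** In section 2.2:

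- State the power of 30 completers for d = 1.5 at the alpha that section 2.9 will apply.
- Name the SD that defines d (single time point, change score or other) and the correlation or variance components entered in the software.
- Do not state 80% power for d = 1.06 and 98% for d = 1.5 unless the authors confirm that the plain 48 h comparison was the basis.

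Make the sizing alpha and the analysis alpha agree. One way is to compute power at the corrected alpha and name the correction. Another, as an option, is a fixed test order, for example AY-BOCS first at 0.05 and then VAS at 0.05 only if AY-BOCS succeeds. This keeps the alpha of 2.2, but VAS cannot be claimed if AY-BOCS fails.

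The cost is one reworded paragraph in 2.2 and one sentence in 2.9. Enrolment does not change.

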To evaluate feasibility and tolerability, the following metrics will be tracked and reported. Specifically, we will report the total number of participants screened, found to be eligible, enrolled, had their enrollment confirmed, and randomized. We will also report on the total number of participants who were found to be ineligible, who voluntarily withdrew from participation prior to randomization, and who were excluded from participation due to safety concerns. In order to evaluate the restrictiveness of our eligibility criteria, we will report the number of participants excluded on the basis of different sets of criteria. Additionally, we will report the follow-up rates (i.e., number of participants who completed follow-up divided by the number of enrolled participants) by treatment arm for all study visits up to 12 weeks post-dosing. Number and percentage withdrawal from the trial with reasons for withdrawal will be summarized at each follow-up and by treatment arm. We will also summarize the number and percentage of participants with missing data for primary and secondary outcomes as a whole and by treatment group and follow-up intervals up to 12 weeks post-dosing. We will employ descriptive statistics and, if possible, logistic regressions to compare baseline characteristics of completers vs. participants with missing data at each follow-up interval.

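### At the stated 20% attrition, 36 enrolled gives about 29 completers, not 30, and the abstract prints a different enrolment figure (minor correction)

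*Protocol article*

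**What the plan says.** Section 2.2 of the protocol article bases the sample size on a mixed-model calculation. Its inputs are a two-sided alpha of 0.05, 80% power and a standardised effect of 1.5. The result is reported in these terms: "which indicated that a total of 30 participants would be needed to detect a significant group effect at the primary endpoint". The section later makes an allowance for dropout: "Assuming an attrition rate of 20%, we plan to enroll 36 participants to ensure 30 completers".

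The abstract, under Methods and analysis, says: "We are enrolling 30 adult participants at a single site in Connecticut, USA". It does not mention 36 and does not say that 30 refers to completers.

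Section 2.4.1.1 lists feasibility counts, including participants "found to be eligible, enrolled, had their enrollment confirmed, and randomized", so enrolment and randomisation are reported as separate stages. The same section also defines follow-up rates by treatment arm with enrolled participants as the denominator.

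**The concern.** The sentence in section 2.2 offers 36 as the number that secures 30 completers at a named attrition rate. A reader can check this in one line, and it fails. The abstract and section 2.2 also use the same verb, to enrol, with two different numbers, so the enrolment target is not uniquely stated.

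What is at stake is the accuracy and consistency of a core reported figure. Feasibility is an explicit aim of the trial, and recruitment and completion will be judged against the published target. If the trial stops at 30 or at 36 enrolled, readers should be able to say whether that target was met.

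**Working it through.** **Inputs** (all from the protocol article)
- Required number: 30 in total (section 2.2)
- Attrition: 20% (section 2.2)
- Planned enrolment: 36 (section 2.2); 30 (abstract)
- Allocation: 1:1 (section 2.1)
- Two-sided alpha 0.05, power 0.80, d = 1.5 (section 2.2)

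**Step 1. Reproduce the plan's figure.** 30 × (1 + 0.20) = 36. This matches exactly. The article shows no formula, so the match is consistent with multiplying by 1.2 but does not prove it.

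**Step 2. Expected completers from 36.** 36 × (1 − 0.20) = 28.8, about 29.

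**Step 3. Enrolment for 30 expected completers.** 30 / (1 − 0.20) = 37.5, rounded up to 38 (19 per arm). Check: 38 × 0.80 = 30.4.

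**Step 4. Attrition that 36 can absorb.** 1 − 30/36 = 16.7%.

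**Step 5. How far 30 is assured.** Assume that each participant drops out independently with probability 0.20 and that every dropout counts against the 30. The binomial probability of at least 30 completers is then 0.40 from 36 enrolled and 0.66 from 38. Even 38 gives 30 only on average.

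**Step 6. Effect on power.** This step uses a simple two-sample t-test at two-sided alpha 0.05 and d = 1.5.

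| Completers | Power | Detectable d at 80% power |
|---|---|---|
| 15 + 15 | 0.977 | 1.06 |
| 14 + 15 | 0.973 | 1.08 |
| 14 + 14 | 0.968 | 1.10 |

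If alpha is halved to 0.025, as one possible correction for the two symptom measures, power is 0.953 at 15 + 15 and 0.937 at 14 + 14.

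This test is a stand-in. For 80% power at d = 1.5 it needs only about 8 to 9 per arm, so it does not reproduce the plan's 30. The variance and correlation inputs and the alpha correction behind the mixed-model calculation are not given. The table therefore shows that losing one completer makes little difference on this test. It is not the plan's own power.

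**The case against.** The strongest reply is that the discrepancy has almost no consequence. It amounts to 1.2 expected completers, the change in detectable d from 1.06 to at most 1.10 lies wholly below the planned 1.5, and power on the simple test barely moves. This stands, and it settles the grade of the point.

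A second reply is that completers do not define the analysis set. Section 2.9 specifies a mixed model with restricted maximum likelihood in order to handle missing data, so participants with partial data can contribute. The primary endpoint is at 48 h, within the 5-day inpatient stay, while follow-up runs to 12 weeks, and section 2.2 does not say when the 20% is lost. If part of it falls after 48 h, the loss at the primary endpoint is smaller. This also stands, and it means that the 0.40 in Step 5 holds only under the assumptions given there.

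Three stronger readings are tempting, and the article does not support them:
- **The trial is underpowered.** Nothing in the article shows this, and the simple test points the other way.
- **The trial will finish with 24 completers** (30 × 0.80, taking the abstract literally). The abstract's 30 most plausibly repeats the required sample from section 2.2. Even at 12 + 12 the simple test gives 0.94.
- **Losses before randomisation come out of the same 36.** Section 2.4.1.1 lists enrolment before randomisation, but it also computes follow-up by arm over enrolled participants, which treats the enrolled as having an arm. The term is used loosely, so this is one possible reading only.

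None of these replies makes the sentence in section 2.2 correct or reconciles it with the abstract.

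**Conclusion.** The point holds as a minor correction of a stated figure. At 20% attrition, 36 enrolled gives about 29 completers; 30 would need 38; and 36 matches 30 completers only at 16.7% attrition. That part is arithmetic on the article's own numbers and rests on no outside assumption. The abstract's enrolment figure of 30 conflicts in wording with the 36 in section 2.2. It is probably the completer target without its label, not evidence of a smaller trial.

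The size is about one completer, or two enrolled participants. The statement that power is little affected rests on the two-sample t-test used in place of the mixed model.

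**What to change.** In section 2.2, make the three figures agree in one of these ways:
- Keep 36 and 20%, and say that about 29 completers are expected.
- Keep 36 and 30, and give the assumed attrition as about 17%.
- Keep 20% and 30, and raise enrolment to 38. This is needed only if 30 completers is a binding requirement.

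In the first and third cases, describe the number of completers as expected, not assured.

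In the abstract, either label 30 as the target number of completers or give the enrolment number used in section 2.2. If the first option is taken, the label should make clear that 30 is the required number and about 29 the expected one.

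The 36 should not simply be relabelled as randomised. Because enrolment is used loosely in section 2.4.1.1, that could change the plan instead of clarifying it. The sponsor should say which stage the 36 counts.

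The first two options cost wording only. The third costs two more participants.
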